## Analysis

Statistical analysis for the CCA and CEA will be conducted using I-WOTCH’s individual patient data (IPD) collected on resource use and outcomes, analysed on an intention-to-treat (ITT) basis. Statistical analysis and decision models will be implemented in R.^33^

### Within-trial cost-consequences analysis

The CCA will focus on estimating and reporting mean health outcomes, resource use and costs by treatment arm at each follow-up interval. No incremental analysis will be conducted. Total costs will be the sum of the costs of the healthcare resource items (described in table 1) that patients used during the study period, plus the cost of either the I-WOTCH intervention or the usual care. Mean health outcomes will include those described in the Identification, measurements and valuation section and be reported at each follow-up period by treatment arm.

#### Handling missing data

We will assess the extent of missing data in the patient-level costs and health outcomes collected during I-WOTCH’s 12-month follow-up and apply appropriate methods to handle the issue following the recommendations by Faria *et al.*
34

#### Statistical analysis

Descriptive statistics (ie, mean, SD, lower and upper quartiles, minimum and maximum values) for all continuous variables reported in table 1 plus total costs will be estimated by trial arm. Histograms and/or box-plots will be used to represent these variables graphically. Binary and categorical variables will be represented in terms of percentages. The impact of patient’s baseline characteristics (ie, age, gender, pain severity, opioid use, duration of opioid intake and opioid medication-related pain condition) as predictors of outcomes will be explored in a series of regression models fitted to ADL, ShOWS, EQ-5D-3L utility scores and cost data to inform the estimation of the Markov model’s input parameters.

We will map EQ-5D-5L utility scores into EQ-5D-3L utility scores.^24 26^ To account for idiosyncrasies of the EQ-5D-3L (ie, multimodality, truncated support and left-skewness), we will use a series of regression models (including mixture of beta models, adjusted limited dependent variable mixture models, two-part models). Each model goodness of fit and assessment of their predictive ability will be carried out using the methods recommended by Hernandez *et al.*
35 36

Many methods have been used to analyse cost data.^37^ We will use generalised linear models (with Gaussian or gamma distributed errors and identity or log links) and where necessary, two-part extensions of these models to account for any mass at zero, the right skewed nature of the dependent variable and possible heteroskedasticity. Should administrative censoring (due to patients’ differential follow-up) be present, the analysis will use inverse probability weighting methods alongside our cost-regression models.^38^

All regression models will explore the impact of the patient’s baseline characteristics included in table 1, and use these results to explore the role of patients’ heterogeneity onto the cost-effectiveness results (more in the Subgroup analysis section).

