## Methods

### Study details (population, setting, location, intervention and comparator)

A detailed study protocol for the I-WOTCH trial has been reported in a separate manuscript.^19^ Briefly, I-WOTCH is a multisite, patient-centred, open RCT enrolling adult patients with non-malignant chronic pain in England. The trial’s target sample size is 542 participants, individually randomised (1:1) to receive the I-WOTCH intervention or best usual care. The I-WOTCH intervention is an 8–10 weeks’ course—consisting of a mixture of group sessions led by two trained I-WOTCH facilitators, two one-to-one individual sessions and two telephone consultations with the I-WOTCH-trained nurse facilitator—adjunct to best usual care. Best usual care consists of general practitioner (GP) care with relaxation package and a booklet called ‘My Opioid Manager’.

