#### Microcosting of I-WOTCH intervention

A microcosting of the resources required to provide the I-WOTCH intervention will be conducted. A detailed description of the categories of resource use to be considered, their associated unit costs and the data collection forms used in the I-WOTCH microcosting exercise is provided in the online supplemental tables A1‒4. Salary, facility and travel costs will be assumed to be independent of the number of participants. Salaries for the facilitators and trainers will be estimated based on average daily salary by grade. The facility costs will be calculated based on the number of venues hired, number of days hired and daily venue hire rate. Travel costs will be considered as fixed cost per mile. Unit costs for nurses’ time for face-to-face and telephone consultations will be extracted from the PSSRU 2019.^28^ A per participant, locality and course cost of I-WOTCH intervention will be reported.

10.1136/bmjopen-2020-037243.supp1Supplementary data

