#### Probabilistic sensitivity analyses

Sampling uncertainty in the model will be captured by characterising each model parameter with an appropriate probability distribution. We will derive the parameters to inform these distributions from the variance–covariance matrix obtained from each regression model. Cholesky decomposition of each variance–covariance matrix will be used to make the simulation more efficient. Sampling uncertainty will be propagated through the model using Monte-Carlo simulation in the form of PSA to understand the effect on the predicted mean QALYs and mean costs associated with each treatment arm. These parameters will then be combined and compared against a range of feasible cost-effectiveness thresholds to obtain an estimate of the probability that I-WOTCH is cost-effective. This information will be represented graphically in the form of a cost-effectiveness acceptability curve.^41^ Also, we will perform scenario analyses for the various distributional assumptions made, for example, on the parametric survival distribution and compare the results for different assumptions.

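### No course or facilitator term, and no cluster-robust variance, is named for the regressions that supply the PSA uncertainty, although one arm is treated in group courses

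*Protocol article*

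**What the plan says.** All references are to the protocol article.

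- Study details: the trial has a "target sample size is 542 participants, individually randomised (1:1) to receive the I-WOTCH intervention or best usual care". The I-WOTCH course is described as "consisting of a mixture of group sessions led by two trained I-WOTCH facilitators", with individual sessions and telephone consultations added. On the other side, "Best usual care consists of general practitioner (GP) care with relaxation package" and a booklet.
- Statistical analysis (within-trial analysis): for costs, "We will use generalised linear models (with Gaussian or gamma distributed errors and identity or log links"), with two-part extensions where needed. For utilities, a series of models "including mixture of beta models, adjusted limited dependent variable mixture models, two-part models". The named predictors are patient baseline characteristics.
- Populating model parameters: transitions between living states come from time-to-event or logit regressions, state costs and utilities from the models above, and the covariance matrix of each regression informs the PSA.
- Probabilistic sensitivity analyses: "We will derive the parameters to inform these distributions from the variance–covariance matrix obtained from each regression model".
- Microcosting of I-WOTCH intervention: "A per participant, locality and course cost of I-WOTCH intervention will be reported".
- Sensitivity analysis (within-trial analysis): minimum against actual number of group sessions, and the smallest and largest observed course, are examined for the cost-consequences analysis.

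**The concern.** Patients who attend the same course share its sessions and its two facilitators. If some courses or facilitators do better than others, tapering, utility and resource use will be correlated among those patients. Usual-care patients have no such grouping. This is correlation between different patients in one arm only, and it arises after individual randomisation. It is separate from repeated measures on one patient and from correlation between equations.

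A covariance matrix that ignores this correlation is too small for parameters estimated from I-WOTCH patients. Because the plan names these matrices as the source of PSA uncertainty, the shortfall passes into the lifetime model. A result driven by a few good or poor courses would then look more certain than it is, and the acceptability curve would be somewhat too steep. The concern is about precision; no bias in the incremental cost-effectiveness ratio is claimed.

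**Working it through.** The plan has no figure of its own to reproduce. The article gives no course size and no intra-course correlation, and the inputs to the sample size of 542 are not in it. The check has two parts.

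**Following the variance through the plan**

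1. Groups exist in one arm only (Study details).
2. The Statistical analysis section lists the data features that its models must handle: multimodality, truncated support, skewness, excess zeros, unequal variance and censoring. Correlation within course is not among them. Table 1, from which covariates are drawn, has no course, facilitator or locality field.
3. No random effect, cluster-robust variance or cluster bootstrap is named for any regression, including the transition regressions.
4. The covariance matrices of these regressions supply the PSA distributions. The scenario analyses in the PSA section concern distributional assumptions and do not fill the gap.
5. Table 2 takes remaining in IT, IT to long-term opioid therapy (LTOT), and IT to successful opioid-less management of pain (SOLMP) from the nurse tapering plan and nurse record form. Only I-WOTCH patients can enter IT, so no usual-care data dilute the clustering in these parameters.

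**Size for quantities resting on I-WOTCH patients alone**

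Inputs: 542/2 = 271 patients in the arm (from Study details); course size m = 8 to 12 and intra-course correlation (ICC) = 0.01 to 0.05 (both assumed).

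Formulas: design effect DE = 1 + (m − 1) × ICC; standard error multiplier = √DE; effective size = 271/DE; true coverage of a nominal 95% interval = 2Φ(1.96/√DE) − 1.

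| m | ICC | DE | SE multiplier | Effective size | Coverage |
|---|---|---|---|---|---|
| 8 | 0.01 | 1 + 7 × 0.01 = 1.07 | 1.034 | 253 | 94.2% |
| 8 | 0.05 | 1 + 7 × 0.05 = 1.35 | 1.162 | 201 | 90.8% |
| 12 | 0.01 | 1 + 11 × 0.01 = 1.11 | 1.054 | 244 | 93.7% |
| 12 | 0.05 | 1 + 11 × 0.05 = 1.55 | 1.245 | 175 | 88.5% |

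Standard errors are therefore about 3% to 24% larger than an unadjusted fit would give. Over a wider assumed range (m = 6 to 12, ICC = 0.01 to 0.10), DE runs from 1.05 to 2.10 and the increase from 2.5% to 45%.

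The formula is for a mean with equal course sizes and every patient on a course, so it is an approximation for logit or time-to-event models. Patients who attend no course share no sessions, which lowers the design effect.

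**The case against.** **Silence is not a stated assumption.** A reader might infer that the plan treats patients as independent. It does not say so. The named models could be fitted with a random effect or a cluster-robust variance without contradicting the text, and a condensed article may leave variance estimation to a fuller plan. This limits the wording of the point but does not remove it. The article presents itself as the protocol for the economic analysis, and the companion papers it cites cover the clinical trial and the model's conceptualisation. It goes as far as error distributions, links and Cholesky decomposition, and it fixes the source of PSA variance.

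**Course variation is partly examined.** Course size and number of sessions are varied, and cost by course is to be reported. That stands for intervention cost. The checks belong to the cost-consequences analysis, are deterministic, and do not bear on correlated outcomes or reach the PSA.

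**The arm-level figure does not carry over to the acceptability curve.** One might apply the formula for a difference between two equal arms with clustering in one: √((1.07 + 1)/2) = 1.017 to √((1.55 + 1)/2) = 1.129, or 2–13%. The documents do not support using it here. The within-trial analysis makes no incremental comparison, and the long-term model compares arms through states. LTOT is the starting state for everyone, and PT (patient-driven tapering) and SOLMP are not confined to one arm. LTOT cost and utility draw partly on literature, SOLMP cost is an assumed GP contact, and mortality is from national statistics. This objection stands.

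**Delivery cost is not clearly regression-based.** Because salary, facility and travel costs do not depend on the number of participants, a reader might infer a correlation of 1 within course, and an effective sample equal to the number of courses (271/12 to 271/8, about 23 to 34). Table 2 takes IT cost from the trial's intervention costing, while the text says in general that state costs come from regressions. The route is unclear, so that stronger claim is not supported. What remains is that no course-level distribution for this cost is named for the PSA.

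**The link from patient to course is not stated.** Reporting cost per course makes such a record likely, but Table 1 does not list one. Nor does the article say that one nurse serves a whole course.

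**Conclusion.** The point holds as a gap in specification. The regressions whose covariance matrices drive the PSA are described without any allowance for courses or facilitators, although one arm is treated in groups. Followed as written, the plan leaves course-to-course variation out of the PSA, most directly in the three IT parameters.

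For quantities estimated from I-WOTCH patients alone, the understatement of the standard error is about 3–24% if courses have 8–12 patients and the ICC is 0.01–0.05. Both ranges are assumptions. The effect on the acceptability curve will be smaller because of shared states and literature inputs, cannot be quantified from the article, and is minor if the ICC is low. Nothing here shows that a decision would be reversed. It should be put right because the plan fixes where its uncertainty comes from and the remedy is standard and cheap.

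**What to change.** - For every transition, utility and cost regression that uses I-WOTCH-arm data, specify one of: a course-level random effect in the I-WOTCH arm only (partially nested model); or a cluster-robust variance by course, with each usual-care patient, and each I-WOTCH patient who attended no course, as a cluster of one. Where the beta mixture or limited dependent variable mixture models do not support these, use a bootstrap that resamples courses.
- State that the resulting variance is the one passed to the PSA.
- In the PSA, vary the per-participant delivery cost using the per-course costs already promised in the microcosting section, and state by which route IT cost enters the model.
- Report the number of courses, their sizes and the estimated ICCs.

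Cost: a few sentences in the plan, some extra coding in R, and linking each I-WOTCH patient to a course in the delivery records. No new outcome data are needed. Intervals will be slightly wider and the acceptability curve slightly flatter; if the ICC proves negligible, results will barely change.

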#### Sensitivity analysis

For the purposes of the CCA, we will carry out a per-protocol analysis and compare the results from the ITT. We will calculate the minimum versus actual number of group sessions needed to provide the I-WOTCH intervention to all participants in the intervention group. We will also consider a minimum and maximum number of participants per course observed in the I-WOTCH trial. We will use a one-way or threshold analyses on the assumptions made on estimating the costs.

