### Long-term model-based cost-effectiveness analysis

#### Populating model parameters

Table 2 provides a list of key model parameters and the source for initial values, that is, mean, SD or CI. To estimate all model initial values, we will use IPD from the I-WOTCH trial and GP records as well as any relevant publicly available evidence. Transitions from all model states to death will be extracted from age and sex adjusted all-cause mortality statistics from the ONS.^39^ Transition probabilities between all the other model states will be derived using risk equations from regression models (eg, time-to-event and/or logit-regression models depending on the nature of the transition). Costs and utilities parameters for each of the model states and events will be estimated using the regression models described in the Statistical analysis section. Variance–covariance matrices for each of the regressions will be extracted to inform the parameter uncertainty estimates in the model and used in the probabilistic sensitivity analysis (PSA) as explained in the Probabilistic sensitivity analyses section.

**Table 2 T2:** Model parameters to inform long-term decision analytic model

Transition probability	Sources	Specific details of the fields in source
Remaining in IT	NTP NCRF	Time of withdrawal from IT Time of withdrawal from IT
LTOT to IT	The trial	Proportion of people engaged in IT
IT to LTOT	NTP NCRF	Time of withdrawal from IT Time of withdrawal from IT
IT to SOLMP	NTP NCRF	Time of completely stopping the use of opioids Time of completely stopping the use of opioids
IT to dead state	PL	All-cause mortality data from ONS
Remaining in LTOT	The trial	Number of people who do not engage in IT and remain in LTOT
SOLMP to LTOT	PtQ GPRs	Medication data Prescription data
LTOT to PT	PtQ GPRs	Medication data Prescription data
LTOT to dead state	PL	All-cause mortality data from ONS
Remaining in PT	The trial PtQ GPRs	Number of people who remain in PT over time Medication data Prescription data
PT to LTOT	PtQ GPRs	Medication data Prescription data
PT to SOLMP	PtQ GPRs	Medication data Prescription data
PT to dead state	PL	All-cause mortality data from ONS
Remaining in SOLMP	PtQ GPRs	Medication data Prescription data
SOLMP to dead state		All-cause mortality rates from ONS
**Utility scores**	**Source**	**Specific details of the source**
LTOT	PL PtQ	Utility of opioid therapy^45^ Regression analysis of patient self-reported EQ-5D

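### Within the cost-consequences analysis, non-adherence is examined only by a per-protocol analysis, whose exclusions would probably fall mainly on the I-WOTCH arm

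*Protocol article*

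**What the plan says.** The Analysis section states that data for both the CCA and the long-term cost-effectiveness analysis (CEA) will be "analysed on an intention-to-treat (ITT) basis". The CCA reports means by arm at each follow-up, and its section adds: "No incremental analysis will be conducted".

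The Sensitivity analysis section for the CCA opens with the statement that "we will carry out a per-protocol analysis and compare the results from the ITT". Its remaining items are the minimum against the actual number of group sessions, the smallest and largest course size seen in the trial, and a check of costing: "We will use a one-way or threshold analyses on the assumptions made on estimating the costs". None of these concerns whether a patient attended. Inverse probability weighting appears in the Statistical analysis section, but only for administrative censoring of costs.

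Under Study details, I-WOTCH is a course of group sessions, two one-to-one sessions and two telephone consultations over 8–10 weeks, given on top of best usual care. The comparator reads: "Best usual care consists of general practitioner (GP) care with relaxation package and a booklet called", followed by the booklet's title. It has no sessions.

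In Table 2, the move into I-WOTCH tapering is estimated from the "Proportion of people engaged in IT". Non-engagers stay in the long-term opioid state, and the time of withdrawal from tapering comes from nurse records. The Microcosting section treats salary, facility and travel costs as independent of the number of participants.

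**The concern.** A per-protocol analysis keeps patients who did what their arm required. Here one arm requires a course lasting weeks, while the other requires almost nothing that a patient could fail to do. Removing non-engagers and withdrawers from the I-WOTCH arm leaves their counterparts in the control arm, because nobody can tell which controls would have stayed away. The two sets of means then describe different kinds of patient.

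The plan gives reason to expect that this matters. It allows for non-engagement and for withdrawal at any time, and it treats pain severity and opioid use as possible predictors of outcome and cost. If these also influence who attends, the per-protocol means are confounded.

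Two misreadings follow. The per-protocol means could be taken as the outcome and cost when the course is actually received. In addition, dropping non-attenders could hide the cost of their places, which is incurred whether or not they come.

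**Working it through.** The article gives no engagement rate, prognostic gap or outcome SD, so it has no figure to reproduce. What follows sizes the mechanism under stated assumptions.

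**Inputs**
- From Study details: 542 participants randomised 1:1, so 542 / 2 = 271 per arm.
- Assumed: engaged share e from 0.5 to 0.9.
- Assumed: gap d between would-be engagers and non-engagers in mean outcome without the course, 0.2 to 0.5 SD.
- Assumed: exclusions in the I-WOTCH arm only, and no effect of allocation in non-engagers.

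**Per-protocol contrast.** Let the would-be engager mean without the course be m. The control mean is e·m + (1 − e)(m − d) = m − (1 − e)d. With effect τ in engagers, the I-WOTCH per-protocol mean is m + τ. The per-protocol difference is therefore τ + (1 − e)d, and the error is (1 − e)d. Its direction depends on whether engagers have the better or the worse outlook.

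**Size with no true effect (τ = 0)**

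| e | d (SD) | Error (SD) | Chance of p < 0.05 |
|---|---|---|---|
| 0.9 | 0.2 | 0.1 × 0.2 = 0.02 | 5.6% |
| 0.7 | 0.2 | 0.3 × 0.2 = 0.06 | 9.7% |
| 0.7 | 0.5 | 0.3 × 0.5 = 0.15 | 35% |
| 0.5 | 0.5 | 0.5 × 0.5 = 0.25 | 66% |

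The last column uses a two-sided 5% normal test with SE = √(1/(271e) + 1/271). The plan proposes no such test, so the column only shows how the error compares with sampling noise.

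**In natural units.** With an assumed utility gap of 0.05 to 0.10, the error at e = 0.7 is 0.30 × 0.05 = 0.015 to 0.30 × 0.10 = 0.03. Over e = 0.9 to 0.5 it runs from 0.1 × 0.05 = 0.005 to 0.5 × 0.10 = 0.05. With an assumed gap of £1000 a year in NHS cost, it is £300 at e = 0.7, and £100 to £500 over the same range of e.

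**With a true effect.** Take τ = 0.30 SD and e = 0.7. ITT gives 0.7 × 0.30 = 0.21. Per-protocol gives 0.30 + 0.06 = 0.36 to 0.30 + 0.15 = 0.45. The complier-average effect, ITT / e = 0.21 / 0.7, returns 0.30.

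**Complier means by arm.** In the I-WOTCH arm this is the observed engager mean. In the control arm it is [control mean − (1 − e) × mean of I-WOTCH non-engagers] / e. The difference between the two equals ITT / e, and every randomised patient is used.

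**Why the course cost must be kept out.** Suppose each I-WOTCH patient carries fixed cost C, and t is the effect on other costs in engagers. The ITT cost difference is C + e·t, so dividing by e gives C/e + t. The cost effect in compliers is C + t. The overstatement is C/e − C = C(1 − e)/e. At e = 0.7 this is 0.30 / 0.70 × C, about 0.43C. It ranges from 0.11C at e = 0.9 to C at e = 0.5. Charging the course to non-engagers means that allocation does change their cost, which breaks the assumption behind the division.

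**The case against.** The case for leaving the plan alone is substantial. A per-protocol analysis beside a primary ITT analysis is conventional. The CCA excludes a formal incremental comparison, so the error sized above lies in a contrast that the plan does not calculate. The per-protocol set is not defined here, and that definition is commonly left to the full protocol or the analysis plan. All of this stands, and it limits the harm. It does not remove the point, because means shown by arm will be read side by side, and a definition given elsewhere could hardly create a course for controls to miss.

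A reader might infer more than the documents support:

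- *That the whole economic evaluation leaves non-engagement to a per-protocol analysis.* It does not. The CEA, where the cost-effectiveness comparison is made, has transitions for engaging, not engaging and withdrawing. These patients stay in the model, and every parameter has a distribution in the probabilistic sensitivity analysis. The per-protocol analysis is stated for the CCA only.
- *That the analysis is known to compare completers with nearly all controls.* This is an inference from what each arm involves. The article gives neither a definition nor adherence figures.
- *That lack of blinding is the cause.* The trial is described as a "multisite, patient-centred, open RCT enrolling adult patients with non-malignant chronic pain in England", but the one-sided selection comes from the difference in what must be attended.
- *That non-attenders' course costs will be dropped.* The article does not say so, and its checks on course size and session numbers partly address how fixed costs are spread.

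One further limit concerns the remedy. Table 2 records engagement and withdrawal separately, so a patient who engages and then leaves counts as engaged. A complier analysis on engagement estimates the effect of engaging, not of completing.

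**Conclusion.** The point holds in a narrow form and is minor. Within the CCA, the one stated sensitivity analysis for non-adherence would probably select mainly on the I-WOTCH side, so its means by arm would no longer be a randomised comparison. That conclusion rests on the contrast between an attended course and usual care without sessions. The size cannot be settled from the article: under the assumptions used, the error runs from 0.02 SD, which is negligible, to 0.25 SD, which is material. It is small if engagement is near 90% and could matter at 50% to 70%. The documents do not show that the ITT results or the long-term cost-effectiveness result are affected.

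**What to change.** In the CCA Sensitivity analysis section, in place of or beside the per-protocol analysis:

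1. Report a complier-average analysis for EQ-5D, PROMIS, ShOWS and NHS costs other than the course. Use random allocation as the instrument and engagement as already recorded for Table 2. Present it as complier means by arm, which fits the CCA format.
2. Add the full fixed course cost separately for all I-WOTCH patients. Do not divide it by the proportion engaged.
3. Label any retained per-protocol means as non-randomised.
4. State that the estimate concerns engagement, so that it is not read as the effect of completing the course.

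This is a wording change and a short extra analysis in R on data already being collected. The price is wider intervals, and the assumption that allocation has no effect on outcomes or other costs in those who never engage.
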